### **Specific Aims:**

1) In comparison to daily leucine supplementation, we aim to examine the impact of dileucine on the observed changes in strength, power, and body composition after eight weeks of supplementation and heavy resistance training.

2) In comparison to placebo supplementation, we aim to examine the impact of leucine and dileucine on the observed changes in strength, power, and body composition after eight weeks of supplementation and heavy resistance training.

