### **Independent Variable**

Supplementation Status:

- 2 grams Dileucine (n=12)
- 2 grams Leucine (n=12)
- Placebo (n=12)

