**STATISTICAL ANALYSIS:**

All analyses will be completed using Microsoft Excel and the Statistical Package for the Social Sciences (v23; SPSS Inc., Chicago IL). Before any statistical tests are performed, data will be analyzed for normality, skewness, and kurtosis. All non-normal data will be log-transformed prior to analysis. For all statistical tests, data will be considered statistically significant when the probability of a type I error is 0.05 or less. Primary endpoints for this investigation will be considered to be the delta (Week 10 – Week 2) value for DEXA fat-free mass and leg press 1RM. Secondary endpoints will be delta (Week 10 – Week 2) values for DEXA fat, DEXA lean and DEXA % fat along with bench press 1RM, bench press repetitions to fatigue, leg press repetitions to fatigue, leg press volume, peak anaerobic power, mean anaerobic power, and rate of fatigue. 2 x 2 mixed factorial (group x time) ANOVA with repeated measures on time will be used to determine any statistically significant differences for time and group main effects and group x time interaction effects. Additionally, 95% confidence intervals will be constructed of the observed changes for each group to assess within and between-group changes. All data will be presented as means  $\pm$  standard deviations.

\*required

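### Alongside the group-by-time ANOVA, intervals for each arm's own change are given a between-group role that they cannot fill, and they are the only stated tool that could be read pairwise

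*Protocol*

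**What the plan says.** The protocol's Statistical Analysis section sets out two steps. First, a "2 x 2 mixed factorial (group x time) ANOVA with repeated measures on time will be used to determine any statistically significant differences" in time, group and their interaction, with the criterion that "data will be considered statistically significant when the probability of a type I error is 0.05 or less". Second, introduced as an addition, "95% confidence intervals will be constructed of the observed changes for each group to assess within and between-group changes".

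The outcome is a change score: "Primary endpoints for this investigation will be considered to be the delta (Week 10 – Week 2) value for DEXA fat-free mass and leg press 1RM".

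Both Specific Aims compare arms. The first reads "In comparison to daily leucine supplementation, we aim to examine the impact of dileucine on the observed changes in strength, power, and body composition"; the second, "In comparison to placebo supplementation, we aim to examine the impact of leucine and dileucine". The Independent Variable section lists dileucine, leucine and placebo with 12 participants each. All three follow the same ten-week training programme (Experimental Design).

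The document gives no SD, no expected change, no pairwise contrast, and no rule for turning the per-group intervals into a between-group statement.

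**The concern.** The aims ask how much more one arm changes than another. The quantity that answers this is the difference between two mean changes, with its own standard error. An interval for one arm's change answers another question: did that arm change at all? All arms train, so some within-arm improvement is expected with or without a supplement effect.

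Per-group intervals can be turned into a between-group reading in two common ways, and the two fail in opposite directions:

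- **Exclusion of zero.** One arm's interval excludes zero, the other's does not, and this is taken as a supplement effect. Identical arms can produce this pattern often.
- **Overlap.** The two intervals overlap, and this is taken as no difference. Real differences are then missed, because non-overlap is much stricter than a 5% test.

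At stake are the pairwise conclusions. With three arms, an overall interaction test does not say which arm differs from which, so a reader turning to the pairwise aims would find only the per-group intervals.

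**Working it through.** There is no power or precision figure in the protocol to reproduce. The check is how per-group intervals behave when read between groups.

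**Inputs from the protocol.** n = 12 per arm (Independent Variable); 95% intervals and a 0.05 criterion (Statistical Analysis).

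**Assumptions, because the protocol is silent.** Two-sided testing; normally distributed changes; the same SD of change in every arm, set to 1; all 12 per arm analysed; a common true change d, in SD units, varied from 0 to 1.5.

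**Critical values.** t(0.975; 11) = 2.201 for one arm's interval; t(0.975; 22) = 2.074 for a difference between two arms.

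**Reading 1: one interval excludes zero, another does not.** Let p be the probability that one arm's interval excludes zero. It comes from the noncentral t distribution with 11 df and noncentrality d√12. For identical, independent arms:

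- two arms disagree with probability 2p(1 − p);
- three arms are not all alike with probability 1 − p³ − (1 − p)³.

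| Common change d (SD) | p | Two arms disagree | Three arms disagree |
|---|---|---|---|
| 0 | 0.050 | 9.5% | 14% |
| 0.4 | 0.245 | 37% | 55% |
| 0.6 | 0.475 | 50% | 75% |
| 0.8 | 0.714 | 41% | 61% |
| 1.0 | 0.883 | 21% | 31% |
| 1.2 | 0.965 | 7% | 10% |
| 1.5 | 0.997 | 0.6% | 0.9% |

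For d = 0.6: 2 × 0.475 × 0.525 = 0.499, and 1 − 0.107 − 0.145 = 0.748. A simulation with 400,000 replicates per scenario agrees (0.499 and 0.748).

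Example with sample SDs of 1: the half-width is 2.201/√12 = 0.635. Observed changes of 0.7 and 0.5 SD give intervals of (0.06, 1.34) and (−0.14, 1.14). One excludes zero and the other does not. The difference is 0.2, with half-width 2.074 × √(2/12) = 0.847 and interval (−0.65, 1.05), p = 0.63.

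**Reading 2: the intervals must not overlap.** With equal sample SDs:

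- non-overlap needs an observed difference above 2 × 0.635 = 1.27 SD;
- the interval of the difference excludes zero from 0.85 SD;
- as a t statistic, non-overlap needs 2.201 × √2 = 3.11 on 22 df, that is p = 0.005.

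With the SDs estimated separately in each arm, the simulated false-positive rate is 0.0054 to 0.0056. Simulated power is 30% against 65% at a true difference of 1.0 SD, and 46% against 80% at 1.2 SD; the first figure in each pair is for non-overlap and the second for the test of the difference.

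Example: observed changes of 0.3 and 1.3 SD give (−0.34, 0.94) and (0.66, 1.94), which overlap. The difference of 1.0 has interval (0.15, 1.85), p = 0.023.

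**The case against.** The strongest reply is that the protocol already contains a valid comparison of change between arms. With two time points, the group-by-time interaction is equivalent to a one-way ANOVA on the change scores, and the 0.05 criterion belongs to the tests. The intervals come only as an addition. This stands. A reader might infer that the trial judges its arms from per-group intervals alone; the text does not support that. The ANOVA is labelled 2 x 2 although there are three arms, but that is a separate matter and this point does not rest on it.

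A second reply is that the protocol names neither reading rule, so the percentages above describe possible misreadings and are not error rates of the stated analysis. This also stands. The wording may be loose shorthand for intervals on both the changes and their differences. As written, however, the intervals are for each group, and their stated purpose includes between-group assessment.

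A third reply is that the size depends on an unknown. It does: for a large common training effect the disagreement between identical arms almost vanishes (10% for three arms at 1.2 SD, under 1% at 1.5 SD). A reader might infer that false signals will be frequent; the protocol gives no SD or expected change from which to conclude that.

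Finally, pairwise contrasts are commonly left to an analysis plan, so their absence alone is not a defect. The point is narrower: the protocol does state a tool for between-group assessment, and that tool is unsuitable.

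**Conclusion.** The point holds in a limited form. The protocol has a valid overall comparison of change in the interaction test. It then assigns a between-group role to intervals that describe each arm separately, and because it names no pairwise contrast, these are the only stated tool that could be read against the pairwise aims.

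The size depends on which reading is used and on the unknown common change. Under exclusion of zero, identical arms disagree in anything from under 1% to about 50% of two-arm comparisons, and from about 1% to about 75% for three arms, with the peak near 0.6 SD. Under non-overlap, the criterion is about ten times stricter than the declared one (0.005 against 0.05), and the observed difference must be about 1.5 times as large (1.27/0.85). All of this assumes normal changes, equal SDs and 12 analysed per arm. It does not show that the trial's main test is invalid or that false claims are likely. It is worth correcting because the sentence invites wrong pairwise conclusions and is easily repaired.

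**What to change.** Replace the sentence on confidence intervals with wording such as:

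> In addition to the group x time interaction test, the between-arm differences in change (Week 10 – Week 2) for dileucine–leucine, dileucine–placebo and leucine–placebo will be reported with 95% confidence intervals; between-group conclusions will rest on the interaction test and these intervals. Per-group intervals of change are descriptive.

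This keeps the planned interaction test and the protocol's own definition of change. It needs no baseline covariate, which would be a different model from the planned ANOVA.

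The cost is one sentence and three contrasts per endpoint from data already planned, with no extra visits or participants. The small downside is that the three pairwise intervals are unadjusted for multiplicity unless the text says otherwise, so it should say which is intended. Under the assumptions above, an unadjusted interval at 12 per arm has a half-width of about 0.85 SD, with power of about 65% for a true difference of 1.0 SD and 80% for 1.2 SD. The pairwise results will therefore remain imprecise.

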## What are your study procedures?

---

*Describe all study procedures and protocol elements in chronological order. Be sure to include (no word limit):*

- *Everything you will ask participants to do, and the duration and frequency of these protocol elements. (Lists, tables, or charts may be helpful for complicated studies.)*
- *Details regarding all procedures, interventions, and methods of data collection.*
- *Any study design elements such as randomizing, blinding, cross-over, etc...*
- *Description of any substances, devices, or equipment used during the study.*
- *If applicable, specify whether each procedure will occur for research purposes or as part of standard of care.*

### Experimental Design

The study will be conducted using a randomized, double-blind approach with individuals being provided daily 2-gram doses of leucine, 2-gram doses of dileucine, or a placebo. Daily blinded supplementation will occur each day for a 10-week period of time while completing a heavy resistance training program. Dosing on workout days will occur within 60 minutes of completing each workout while doses on non-workout days will be ingested with their morning meal. On workout days, assigned dosing will be ingested within 60 minutes of completing their workout and on-days when study participants complete a workout at university facilities, the assigned supplement will be consumed in front of a research team member. The resistance training protocol will follow a linear periodization, split-body resistance training design consisting of two upper body and two lower body workouts each week resulting in each muscle group being trained twice each week. To minimize the influence of training experience and any learning effect, individuals with at least 12 months of resistance training history will be recruited. Participants follow the resistance training program for a total of 10 weeks. To assess the efficacy of the two different forms of amino acid supplementation on resistance training adaptations, changes in fat-free, lean, and fat mass will be determined using a 4-compartment body composition model. Skeletal muscle cross-sectional area will be assessed using ultrasound. Maximal strength will be assessed by determining one-repetition maximums (1RM) for the bench press and leg press exercises in addition to completion of an isometric mid-thigh pull. Muscular endurance will be assessed by determining the maximal number of repetitions completed using 80% of the 1RM (i.e. multiple-repetition maximum [RTF]) determined at baseline. Lower-body muscular power will be assessed using countermovement jumps and anaerobic capacity using a Wingate anaerobic capacity test. Participants will also be provided nutritional recommendations to ensure adequate energy and macronutrient consumption to facilitate positive training adaptations and eliminate any potential influence of differing dietary intakes. Participants will be required to provide weekly compliance and complete one supervised workout per week. After 2, 6, and 10 weeks of following the supplementation and resistance training regimens, participants will return to

the laboratory to complete testing bouts consisting of identical assessments of body composition, muscular strength, muscular endurance, lower-body power, and anaerobic capacity. Adverse events related to each supplementation group will be recorded and assessed.

### Familiarization and Entry (Visit 1)

At the first lab visit, participants will receive an informed consent document and will be required to give full consent before proceeding. Upon providing consent, participants will provide personal and emergency contact information before completing a healthy history and exercise history form. Study participants will receive a dietary log and will be asked to record their nutrient intake over a 3-day period (2 weekdays and 1 weekend day) for assessment of daily energy and macronutrient intake. Participants will then have initial height and body mass measurements completed. The body mass assessments taken at this time will be used as a comparison to their Visit 2 body mass to ensure participants are weight stable. To conclude this visit, participants will complete the 1RM protocol on both the bench press and leg press exercises and will complete the mid-thigh pull test, countermovement jump (CMJ) protocol and Wingate anaerobic capacity (WanT) protocol. If screened eligible due to adequate baseline strength, study participants will then be oriented to the resistance training program they will be required to follow throughout the study.

This orientation will consist of a discussion with a research team member on how to properly progress the loads they will use during each workout in addition to completing their training log in addition to discussion what dietary requirements are expected throughout the protocol. Participants will then complete a strength orientation session where an 8 to 10-repetition maximum load will be determined for all exercises they plan to utilize to begin the workout program. In addition, participants will be instructed on how to use their workout card to properly progress loads used during each workout. All participants will be required to log completion of each workout. This study visit is estimated to take 90 minutes to complete.

To document and facilitate compliance, participants will be required to log completion of each workout, send a picture of them in the gym next to exercise equipment, and schedule at least one workout per week to be completed on campus in our laboratory facilities. If individuals want to complete more workouts each week at the facilities housed at our university, they will be accommodated.

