## What disqualifies a participant for your research?

---

*Please include all exclusion criteria.*

25.

- Female
- Participants who are determined to not be weight stable defined as week 0 and week 2 body mass levels deviating by 3% or more.
- Any individual who is currently being treated for or diagnosed with a cardiac, respiratory, circulatory, musculoskeletal, metabolic, immune, autoimmune, psychiatric, hematological, neurological or endocrinological disorder or disease.
- Body mass index  $> 25 \text{ kg/m}^2$ . Individuals with a body mass index greater than  $25 \text{ kg/m}^2$ , but a body fat percentage less than 25% fat will be accepted into the study
- Individuals who present with any previous injury or illness that would prevent them from appropriately completing all exercise lifts.
- Participants who are not able to fit onto the DEXA table will not be able to participate in the research due to size restrictions of the equipment. This typically includes individuals exceeding 400 pounds or those greater than 6'4".
- Those individuals with less than 12 months of structured resistance training experience will be excluded from the study.
- Individuals whose maximal relative upper body strength is below 1.0 will be excluded.
- Individuals whose maximal relative lower body strength is below 1.5 will be excluded.
- All participants who DO NOT abstain from taking any additional forms of nutritional supplementation deemed to be ergogenic or that will impact resistance training adaptations (pre-workouts, creatine, beta-alanine, etc.) for four weeks prior to beginning this study and for the entire duration of the study.
- Individuals who are currently using or have used within the past 12 months anabolic-androgenic steroids.

\*required

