#### Describe any and all physical risks:

---

49e.

*Provide detail regarding the frequency, severity, and duration of each risk.*

-Exposure to radiation through the completion of a DEXA.-BIA assessment poses a near trivial level of risk for someone with a pacemaker or internal defibrillator.-Risks of upset stomach or GI distress from -Risk of exposure to COVID-19 for participants, research team members, and others on Lindenwood's campus who may come in contact with them.-Risk of privacy during Ultrasound-Risk of injury from performance testing and/or resistance training program

\*required

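### Visit 1 applies the strength criteria only after the whole test battery, so men who fail on 1RM would still do an all-out Wingate that serves no purpose for them

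*Protocol*

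**What the plan says.** In the Protocol, Familiarization and Entry (Visit 1), height and body mass are measured after consent and history. Then "participants will complete the 1RM protocol on both the bench press and leg press exercises and will complete the mid-thigh pull test", followed by the "countermovement jump (CMJ) protocol and Wingate anaerobic capacity (WanT) protocol". The eligibility sentence comes next: "If screened eligible due to adequate baseline strength, study participants will then be oriented to the resistance training program". After the orientation there is a strength session in which "an 8 to 10-repetition maximum load will be determined for all exercises they plan to utilize to begin the workout program". The paragraph ends with an estimate of 90 minutes, yet the test battery was introduced as the closing part of the visit.

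The exclusion criteria (Question 25) state "Individuals whose maximal relative upper body strength is below 1.0 will be excluded" and "Individuals whose maximal relative lower body strength is below 1.5 will be excluded". Neither names the test. The physical risks (Question 49e) include "Risk of injury from performance testing and/or resistance training program". Table 1 marks 1RM, mid-thigh pull, jump and anaerobic capacity at Visit 1.

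**The concern.** The strength criteria appear to need only the two 1RMs and body mass, all available before the Wingate. Placing the check after the full battery means that a man already known to be ineligible is asked for further maximal efforts. For enrolled men these tests serve as familiarisation before the Visit 2 baseline. For an excluded man they serve neither familiarisation nor any analysis. What is at stake is avoidable exposure to a risk that the protocol itself lists.

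The section is also unclear about what Visit 1 contains. It presents the test battery as the end of the visit, then describes an orientation and a load-setting session, and only then gives the duration.

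**Working it through.** **1. What the criterion needs.** The Maximal Strength section uses bench press as the upper-body test and leg press as the lower-body test. I assume that relative strength means 1RM divided by body mass, with limits 1.0 and 1.5. Body mass is taken earlier in the visit, so both ratios are known once both 1RMs are done. The Experimental Design section also counts the mid-thigh pull as a test of maximal strength. Even if the pull informed the criterion, the Wingate would not.

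**2. Which tests could be avoided.** The Visit 1 text gives an order of listing. The Visit 2 text gives an explicit sequence.

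| Order | Before both 1RMs are known | After both 1RMs are known |
|---|---|---|
| As listed for Visit 1 | none | pull, jumps, Wingate |
| As sequenced for Visit 2 | jumps, pull | Wingate |

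The Wingate comes last in both, so it is avoidable under either order.

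**3. Use of the Visit 1 results.** The Statistical Analysis section defines its primary and secondary endpoints as Week 10 minus Week 2. No endpoint uses a Visit 1 pull, jump or Wingate value.

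**4. Number affected.** Let f be the share of otherwise eligible men who fail on strength. To enrol 36, the number who fail is 36 × f / (1 − f). The protocol gives no value for f, so these are assumptions:
- f = 0.20: 36 × 0.20 / 0.80 = 9
- f = 0.40: 36 × 0.40 / 0.60 = 24

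The requirement of 12 months of structured training may put f below this range.

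**5. The 90 minutes.** The figure cannot be reproduced, because no times are given for consent, forms, orientation or load setting. The rests and warm-ups can be added up if the Visit 2 details are assumed to hold at Visit 1.
- Each 1RM, low (three attempts, only the rests stated): 2 + 2 × 2 + 3 = 9 min.
- Each 1RM, high (five attempts, 2 min also between the warm-up sets): 2 + 4 + 2 × 4 + 3 = 17 min.
- Other items: five jumps 4, three pulls 2, Wingate 5.5, cycling warm-up 5, together 16.5 min.
- Total: 2 × 9 + 16.5 = 34.5 min to 2 × 17 + 16.5 = 50.5 min.
- Remainder of 90: 39.5 to 55.5 min.

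Table 2 lists 14 loaded exercises for weeks 1-6 (8 upper body, 6 lower body, crunches left out). The remainder is 39.5 / 14 = 2.8 to 55.5 / 14 = 4.0 min per exercise before any administration. With an assumed 15 to 30 min of administration it is (39.5 − 30) / 14 = 0.7 to (55.5 − 15) / 14 = 2.9 min. One visit of 90 minutes looks tight, but the arithmetic does not show it to be impossible.

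**The case against.** The strongest reply is that the Visit 1 text joins the tests in a list and fixes no sequence. Nothing forbids staff from reading the 1RM results and stopping. If Visit 1 follows the Visit 2 order, the jumps and pull are done before the 1RMs and only the Wingate could be saved. Consent comes first, the 1RMs remain under any change, and Question 49f describes the tests as of an intensity that healthy, active people are presumed to manage weekly. Most of this stands and limits the point to the Wingate with certainty. It does not remove the point, because the text lets the criterion gate only the orientation and gives no instruction to stop.

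A reader might infer more, in three ways that the document does not support.

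- **Starting loads are set while fatigued and so are too low.** No rest interval before load setting is stated, and it is unclear whether that session is in the same visit. Fatigue is plausible but inferred. The programme prescribes three sets of ten to failure with one minute's rest, so a load slightly below a fresh 8 to 10RM is not evidently too light. The Load Progression section and the re-assignment from new 1RMs at Visits 3 and 4 would correct an error.
- **The 90 minutes is wrong.** Any excess depends on assumed times for consent, forms and load setting. The form is emailed beforehand when possible, and the figure is called an estimate.
- **The group comparison is affected.** Load setting comes before any supplement is taken, and assignment is double-blind and matched on Visit 2 fat-free mass. Table 1 marks randomisation at Visit 1, but on either timing an error in starting loads should not differ by arm. It also arises before Week 2, where the measured change begins.

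**Conclusion.** The point holds as a minor weakness in sequencing and participant burden. As written, a man who fails the strength criteria on his 1RMs would still do an all-out Wingate, and possibly the pull and jumps, with no use for the results. The size is one avoidable Wingate for each man who fails, or 9 to 24 in all if 20% to 40% fail. It rests on two assumptions: that the criteria are judged on bench press and leg press 1RM relative to body mass, and that staff follow the text as it stands.

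Effects on starting loads and on visit length are plausible but not shown. There is no effect on any endpoint definition and no bias between arms.

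**What to change.** In Familiarization and Entry (Visit 1), state that the two strength criteria are checked as soon as both 1RMs are known, and that only men who meet them go on to any maximal test still to be done, at least the Wingate. This wording leaves the Visit 2 test order available for familiarisation. Naming the two 1RMs and body mass in the exclusion criteria would remove the remaining doubt about how the ratios are formed.

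In the same section, reconcile the wording that presents the test battery as the end of the visit with the orientation and load-setting session that follow. Say whether that session is part of the 90 minutes, and keep the 1.5 hours in the compensation rationale (Question 20b) consistent with the answer.

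Moving load setting is not part of this change. The first supervised workout would cover only the upper-body or the lower-body half of the programme, and loads set just before the Wingate would still follow two 1RMs.

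The cost is a few sentences and a ratio calculated during the visit. No test or staff are added.
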